### Participants

A total of 80 participants aged 18 to 65 years will be recruited, comprising 40 adults with a confirmed diagnosis of ADHD and 40 neurotypical controls.

Adults with ADHD will be recruited through outpatient ADHD clinics in Sligo, Ireland, where psychologists or psychiatrists will identify eligible participants based on a clinical diagnosis according to *DSM-5* criteria. Neurotypical controls will be recruited through community outreach, including advertisements in schools and local public spaces.

Inclusion criteria for all participants include fluency in English and the ability to understand study instructions and complete cognitive assessments. Exclusion criteria for all participants include (1) a history of learning disabilities; (2) severe brain injury causing cognitive impairment; (3) current substance or alcohol abuse; (4) severe medical illnesses or mental illnesses like acute psychosis, mania, or major depression affecting cognitive function; and (5) extended reality–specific contraindications, including a history of epilepsy or photosensitive seizures, diagnosed vestibular disorders (eg, Ménière disease, chronic vertigo, and vestibular migraine), or severe motion sickness or cybersickness that has previously limited engagement with VR or similar technologies. These factors may confound cognitive and EEG outcomes, limiting the interpretability of environmental exposure effects, and are therefore excluded to ensure participant safety. For the neurotypical control group, participants will be excluded if they score above the clinical threshold (≥15) on the General Health Questionnaire-12 (GHQ-12) [66], or if they meet the ADHD screening criteria on the Adult ADHD Self-Report Scale (ASRS) Part A (4 or more responses fall within the darkly shaded boxes, indicating symptoms highly consistent with adult ADHD) [67].

### Exposure Conditions

#### Physical Nature Exposure Condition

Participants assigned to this condition will be escorted to a designated seating area within a forest located near the clinic. They will be instructed to sit quietly for 20 minutes, remain awake, and keep their eyes open. The study will be conducted between April and September, when local weather and daylight conditions in the west of Ireland are relatively stable. Sessions will be scheduled on dry, calm days and, where possible, at comparable times of day to minimize variation in temperature and light.

For each session, the research team will record ambient temperature, weather conditions (eg, sun, cloud cover, wind, or unexpected rain), and notable environmental events (eg, unusual noise or human activity). These contextual variables will be retained for sensitivity and exploratory analyses and will be described as inherent features of the real nature condition. Immediately following the exposure, participants will complete a series of cognitive and emotional assessments outdoors in the same natural setting.

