### Procedures

Participant enrollment will be conducted through a face-to-face clinical interview with a trained psychologist or psychiatrist to confirm the diagnosis of ADHD and assess potential comorbidities based on *DSM-5* (*Diagnostic and Statistical Manual of Mental Disorders, Fifth Edition*) criteria.

Following informed consent and completion of baseline assessments, participants will be stratified by diagnostic status (ADHD vs neurotypical control). Within each stratum, the random allocation sequence will be generated by an independent research coordinator (not involved in recruitment or outcome assessment) using computer-generated permuted blocks of variable size with a 1:1 allocation ratio. This stratified block design ensures balanced group sizes over time and equal distribution of diagnostic groups across conditions.

The allocation sequence will be implemented using sequentially numbered, opaque, sealed envelopes prepared in advance by the independent research coordinator. Treating clinicians or research assistants will enroll participants and open the next envelope only after baseline measures are completed, ensuring that upcoming assignments remain concealed from both participants and enrollment staff. Due to the nature of the intervention condition, blinding of participants and experimenters is not feasible; however, data analysts will remain blinded to group allocation and condition labels until the primary analyses are completed to minimize bias during statistical analysis.

As illustrated in Figure 1, cognitive and emotional assessments will be administered at 10 time points: preexposure (T0), immediately postexposure (T1), and weekly over an 8-week follow-up period (T2-T9). These assessments will be completed online within the study platform. ADHD-specific assessments will be conducted at 3 time points: T0, T1, and the final follow-up (T9). EEG data will be recorded continuously during the exposure session to capture real-time brain activity in response to the environmental condition.

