### Follow-Up Assessments

Existing work on nature exposure largely falls into 2 patterns: single-session studies that examine immediate effects and multiweek intervention programs involving repeated exposure (eg, weekly 45-minute walks in nature), with follow-up data suggesting that some benefits are no longer detectable at 1-month follow-up [64]. Against this background, this study includes an extended follow-up after a single 20-minute exposure to real or VR-simulated nature, delivered via an online survey platform that sends automatic weekly reminders before each assessment to support retention and minimize participant burden.

Beyond the immediate postexposure assessment, participants complete weekly online follow-ups over an 8-week period. The primary rationale for these repeated assessments is to characterize how any acute changes in cognition and mood observed at T1 decay over time. This design allows us to estimate the short-term time course of attenuation and to explore whether the pattern of change differs between exposure modalities and between individuals with different neurocognitive profiles, including varying levels of ADHD symptoms. Such information may help to inform the scheduling and dosing of future nature-based interventions.

In addition, the extended 8-week window provides an opportunity to examine more gradual shifts in lifestyle and nature relatedness. At baseline and at follow-up, we record the frequency and duration of participants’ additional contact with real outdoor nature and VR-based nature experiences, as well as repeated measures of nature connectedness using the Nature Connection Index (NCI) [65]. These data will be used descriptively and in exploratory analyses to assess whether a single experimental session has any downstream impact on everyday nature exposure or perceived connection to nature while also helping to account for ongoing environmental input when interpreting long-term trajectories.

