Secondary outcomes include trajectories of emotional well-being assessed via weekly EMA, clinical functioning in the group with ADHD (ACOS-Self), quality of life (AAQoL), and nature connectedness (NCI). EMA scores over T0-T9 will be modeled with LMMs including fixed effects for time (treated as a continuous or categorical variable depending on fit), condition, group, and their interactions, with random intercepts for participants. ACOS-Self, AAQoL, and NCI change from T0 to T9 will be analyzed using separate LMMs with fixed effects for group, condition, and their interaction. Self-reported real-world nature and VR exposure during follow-up will be explored as time-varying covariates in additional models to probe their contribution to decay or maintenance of effects.

To incorporate a dimensional perspective, *z*-scored ASRS total and subscale scores will be included as continuous predictors in a restricted set of prespecified models [85] (eg, ASRS × condition × time interactions for alpha power and cognitive outcomes). These analyses will test whether attentional trait variation predicts sensitivity to environmental exposure across the full sample, without overparameterizing models.

Multiple-comparison control will be applied at the level of outcome families: EEG (regions of interest and key contrasts), cognitive tasks (Meta Mind and Star Racer indices), EMA trajectories, and clinical measures. Within each family, *P* values will be adjusted using false discovery rate procedures; unadjusted and adjusted values will both be reported.

Model assumptions (normality of residuals, homoscedasticity, and, where relevant, sphericity) will be checked using diagnostic plots and formal tests. If assumptions are violated, transformations or robust alternatives will be considered. Missing data will primarily be handled within the mixed-model framework under a missing-at-random assumption. In addition, sensitivity analyses will be conducted using multiple imputation and complete-case subsets (participants with data at least up to T1 and T9) to examine the impact of attrition on key inferences.

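### Daylight from April to September is not stable, and with no calendar term or unexposed arm the pooled or within-arm 8-week course mixes season with time since exposure

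*Protocol article*

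**What the plan says.** The section on the physical nature exposure condition puts the study "between April and September, when local weather and daylight conditions in the west of Ireland are relatively stable". Each participant is then followed weekly for 8 weeks (T2 to T9). The Follow-Up Assessments section explains why: "The primary rationale for these repeated assessments is to characterize how any acute changes in cognition and mood observed at T1 decay over time". It also proposes to examine "whether a single experimental session has any downstream impact on everyday nature exposure or perceived connection to nature".

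The Statistical Methods section states the models. For mood, "EMA scores over T0-T9 will be modeled with LMMs including fixed effects for time", condition, group and their interactions, with a random intercept per participant. NCI change from T0 to T9 is modelled on group, condition and their interaction. Neither model contains calendar date, month or day length. Nature contact has no stated trend model of its own.

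Three safeguards are stated:
- "Self-reported real-world nature and VR exposure during follow-up will be explored as time-varying covariates in additional models", and the contact data are meant to serve their purpose "while also helping to account for ongoing environmental input when interpreting long-term trajectories".
- Weather is logged at each outdoor session: "These contextual variables will be retained for sensitivity and exploratory analyses".
- Condition is allocated in permuted blocks within diagnostic stratum, and the longitudinal results are labelled exploratory in the Power and Discussion sections.

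**The concern.** Decay is a statement about the time trend itself. Every participant is exposed to nature, real or virtual, so no arm shows what mood, nature connectedness or outdoor contact would have done over the same weeks without a session. If any of these follows the season, a fall after a summer session looks like fading benefit, and a rise after a spring session looks like maintenance or a change in lifestyle.

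The comparison of diagnostic groups over time is open to the same problem under one condition. Adults with ADHD come from outpatient clinics and controls from community advertising. Stratified blocks balance condition within each diagnosis, but they do not align the two groups' entry dates.

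At stake is what the follow-up is meant to supply: a time course to help plan the frequency and dose of later interventions.

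**Working it through.** The article gives no figure for daylight or seasonal change, so there is none to reproduce.

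**Inputs from the article:** window April to September; 8 weeks (56 days) of weekly scores; 80 participants; two-sided α of .05; random intercept in the EMA model. **Assumptions:** latitude φ = 54.3° (the article names Sligo but gives no latitude); mood-daylight slope b of 0.02, 0.05 or 0.1 SD per hour; within-person residual SD σ of 0.63 (ICC 0.6, √0.4) or 0.7; no exposure effect.

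**1. Day length.** Hours = (2/15) × arccos[(sin(−0.833°) − sin φ sin δ) / (cos φ cos δ)], with declination δ = 23.45° × sin(360(284 + n)/365) and n the day of the year.
- 21 June (n = 172, δ = 23.45°): arccos[(−0.0145 − 0.812 × 0.398)/(0.584 × 0.917)] = arccos(−0.631) = 129.1°, so 17.2 h.
- 1 April: 12.9 h. 30 September: 11.5 h.

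A second declination formula gives 13.0, 17.2 and 11.7 h. With it, latitudes from 53° to 55.5° give a spread of 5.2 to 5.8 h.

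**2. Change over one follow-up.** Entry on 1 April: 16.6 − 12.9 = +3.7 h. Entry on 1 September: 9.55 − 13.65 = −4.1 h. (Second formula: +3.6 and −4.0 h.)

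**3. Mean change over entry dates.**
- Sessions spread evenly from 1 April to 30 September: −1.6 h, with 70% of entry dates losing daylight.
- Follow-up also ending by 30 September, so last entry 56 days earlier, on 5 August: −0.57 h.

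**4. Spurious 8-week trend** ≈ b × mean change. For April-September entry: 0.02 × −1.6 = −0.03; 0.05 × −1.6 = −0.08; 0.1 × −1.6 = −0.16 SD. Simulation gave −0.04, −0.08 and −0.17.

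**5. False-positive rate.** The sum of squares of weeks 0 to 8 about their mean is 60, so the SE of an 8-week change is 8σ/√(80 × 60): 0.073 for σ = 0.63 and 0.081 for σ = 0.7. At b = 0.05, 0.08/0.073 = 1.10 gives about 19% rejection, and 0.08/0.081 = 0.99 gives about 17%. Simulations agree:

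| Slope (SD/h) | Entry April-September | Entry to 5 August |
|---|---|---|
| 0.02 | 6-8% | about 5% |
| 0.05 | 17-20% | 6-9% |
| 0.1 | 52-60% | 9-16% |

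The ranges reflect the two residual SDs and simulation error.

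**6. Interactions.** Condition × time stayed near zero, with 3-7% rejection throughout. Group × time was near zero when both groups entered over the same dates. With one group entering 1 April-15 June and the other 16 June-30 September, it was −0.24 (32% rejection) at b = 0.05 and −0.48 (84%) at b = 0.1.

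**7. With day length in the model** (b = 0.1): pooled trend −0.01, rejected in 6%; group × time under split entry 0.01, rejected in 5%. Staggered entry makes day length separable from weeks since exposure.

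**The case against.** Much can be said for the plan.

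- **The daylight phrase is about running outdoor sessions.** No follow-up analysis is said to rely on it. That is so, but the statement is still wrong, and the EMA model terms are set out without any calendar term.
- **The trajectories are exploratory**, to be read by effect size and precision rather than by significance alone. This lowers the stakes. It does not remove a bias in the estimate, and the Discussion still offers these data for planning dose and frequency.
- **Outdoor contact is measured and explored as a time-varying covariate.** A reader might infer that seasonal contact is simply ignored; it is not. But contact does not capture other seasonal routes to mood, may itself respond to the exposure, and cannot adjust itself when it is the outcome. The session weather log describes the exposure day, not the following weeks.
- **Such covariates are often left to an analysis plan.** This is fair for fine detail and is one reason to accept a sensitivity analysis.

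Some stronger readings are tempting but unsupported:
- *The real-versus-VR comparison of decay is biased.* Condition is randomised in permuted blocks, so a season effect common to both arms cancels in expectation.
- *Follow-up runs to late November.* This holds only if sessions continue to the end of September. The sentence speaks of the study, which may include follow-up.
- *Most trials would show a false trend.* Rates near 80% need entry confined to July-September, whereas the article has data collection starting in April.
- *The diagnostic groups will be run in different months.* Nothing says so.

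**Conclusion.** The point holds in limited form. The daylight statement is wrong by a wide margin (about 11.5 to 17.2 h at an assumed latitude of about 54°N). The pooled or within-arm EMA course and the mean T0-T9 NCI change cannot be separated from season as the models stand. Group × time is exposed only if the groups' entry dates differ. Condition × time and the primary T0-T1 contrasts are unaffected.

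The size cannot be settled from the article, because it gives neither a mood-daylight slope nor entry dates. Across the assumed slopes, the false-trend rate runs from near nominal to about 60% if sessions fill April to September, and stays at or below about 16% if follow-up must also end in September. A day-length term brings it to about 5%.

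A reader might infer that a season-adjusted trend would then measure decay. It would not: without an unexposed arm it remains open to regression to the mean, repeated testing and dropout.

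**What to change.** 1. Remove daylight from the stability statement, and say whether April-September bounds the sessions only or the follow-up as well.
2. Add day length on the assessment date, or a smooth calendar-date term, to the T0-T9 EMA model, and the T0-T9 change in day length to the NCI model, at least as a prespecified sensitivity analysis. Use the same term in any trend analysis of nature contact.
3. Enter ADHD and control participants over the same months where feasible.
4. Describe pooled or within-arm trends as uncontrolled even after adjustment, and rest claims about real versus virtual nature on condition × time.

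The cost is one covariate computed from assessment dates, a scheduling note and a slightly wider interval for the time trend. No new outcome data are needed.

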#### Immersive VR Exposure Condition

Participants assigned to this condition will be equipped with the Meta Quest 3 standalone headset and hand controllers. They will engage in a 20-minute immersive simulation of a forest environment, designed to closely approximate the real forest setting used in the physical nature condition. The simulation is delivered through an open-source forest scene compatible with the Meta Quest platform. The VR application is a nonclinical research stimulus and is used solely for experimental exposure in this study. It includes synchronized visual and auditory stimuli (eg, trees and ambient forest sounds such as bird calls) to enhance ecological realism. Immediately following the VR exposure, participants will complete the same assessments as those in the physical nature condition.

#### Exposure Duration

Both exposure conditions use a fixed 20-minute session. This duration was selected to balance efficacy and tolerability, particularly for adults with ADHD. From a safety perspective, a review of temporal aspects of simulator sickness indicates that longer VR exposure is one of the strongest predictors of cybersickness, with more severe symptoms often emerging after approximately 20 to 30 minutes of continuous use [68]. In parallel, work on VR applications for individuals with attentional difficulties suggests that prolonged continuous tasks can lead to vigilance decrement, frustration, and disengagement in people with ADHD [69]. Keeping the exposure at 20 minutes therefore provides a conservative upper bound that aims to minimize the risk of sensory overload and cybersickness while maintaining engagement, especially in the group with ADHD.

At the same time, 20 minutes is sufficient to capture meaningful restorative effects. Although dose-response data for EEG in natural environments are limited, field studies of nature exposure in daily life have shown that approximately 20 minutes in urban green spaces can already produce measurable changes in stress-related biomarkers and autonomic regulation [70]. Given that EEG indexes neural activity on a millisecond timescale, a 20-minute window is expected to provide ample data to observe changes in cognitive processing and brain dynamics during exposure without extending into durations where fatigue and simulator sickness become more common. Taken together, a 20-minute session was judged to offer an adequate “dose” to elicit and measure neural and cognitive responses to real and VR-simulated nature while reducing the likelihood of adverse effects and dropout, particularly among adults with ADHD.

#### Safety and Tolerability Monitoring

All VR sessions will be conducted individually in a quiet room with a researcher present at all times. Before donning the headset, participants will be informed that they may stop the session at any point if they experience discomfort (eg, nausea, dizziness, eye strain, or anxiety) without providing a reason and without any negative consequences. The researcher will visually monitor posture and behavior throughout the 20-minute exposure and will terminate the session immediately if marked distress or instability is observed.

Immediately after VR exposure, participants will complete the Virtual Reality Sickness Questionnaire (VRSQ) [71] to systematically assess cybersickness symptoms. Any adverse events or early terminations will be documented using a standard adverse event form, and participants will be offered rest and, if needed, medical review according to site procedures. Participants who request to stop the session will not be asked to complete any further study procedures at that visit, and no additional outcome data will be collected beyond what has already been obtained.

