Resting-state baselines will be collected preexposure and postexposure (T0 and T1) with 2-minute eyes-open (fixation cross) and 2-minute eyes-closed recordings while participants sit quietly, instructed to stay relaxed, minimize blinking, and avoid large movements. During the 20-minute nature or VR exposure, EEG will be recorded continuously while participants remain seated; they will be reminded that they may pause or terminate the session if they experience discomfort, and any early termination will be documented and treated as dropout for EEG analysis. Evidence from previous VR-EEG studies [83] and from our own pilot testing indicates that simultaneous use of the FLEX cap and the VR headset is safe and allows reliable signal acquisition. Nevertheless, because VR head-mounted display padding can occasionally impinge on frontal or frontopolar sites, headset fitting will follow a predefined substitution protocol: if AF3/AF4 are partially obstructed, frontal alpha asymmetry will be computed from the canonical F3/F4 pair; if Fp1/Fp2 cannot be used, priority will be given to maintaining midline integrity at Fz. For any substituted electrodes, 3D electrode positions will be digitized to allow offline correction of spatial shifts, and the midline chain Fz-Cz-Pz-Oz will be preserved in all participants for core spectral and ERP analyses.

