#### Statistical Methods

All analyses will follow an intention-to-treat approach and will be conducted using R (R Foundation for Statistical Computing). Statistical tests will be 2-tailed with a significance level of α=.05. Descriptive statistics will summarize sample characteristics. Baseline group differences will be assessed using Pearson chi-square tests for categorical variables and independent-samples *t* tests (or nonparametric equivalents) for continuous variables. Any variables showing systematic baseline imbalance will be considered as covariates in sensitivity analyses.

To evaluate the primary outcomes—changes from preexposure (T0) to immediate postexposure (T1) in EEG alpha power, cognitive performance (Meta Mind and Star Racer), and ASRS, we will implement linear mixed-effects models (LMMs) using the *lme4* package. Fixed effects will include exposure condition (real vs VR nature), diagnostic group (ADHD vs neurotypical), time (T0 vs T1, with T9 added where relevant to examine short-term maintenance), and their interactions. Participant will be entered as a random intercept; random slopes for time will be added where supported by convergence and model fit. The primary contrasts of interest are: (1) group × condition × time for alpha power in predefined frontal and parietal regions of interest, and (2) condition × time and group × time interactions for cognitive and ASRS outcomes.

For EEG data, log-transformed alpha power (8-13 Hz) will be averaged within each region of interest and exposure phase. Within-subject change scores (T1-T0, and T9-T0 where applicable) will be analyzed in the LMM framework described above. Exploratory time-resolved effects across the 20-minute exposure will be examined using cluster-based permutation tests on epoch-wise alpha power, with family-wise error controlled at 0.05. Effect sizes will be reported as Cohen *d* for pairwise contrasts and partial eta squared (η^2^_p_) for omnibus tests.

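### VR participants who ask to stop early give no T1 outcomes, so primary data go missing for a reason tied to the assigned exposure

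*Protocol article*

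**What the plan says.** Four parts of the Protocol article bear on this.

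- **Safety and Tolerability Monitoring** (VR sessions). Participants may stop for discomfort such as dizziness, nausea, anxiety or eye strain. Those who ask to stop do nothing further at that visit, and "no additional outcome data will be collected beyond what has already been obtained". The same section says "Immediately after VR exposure, participants will complete the Virtual Reality Sickness Questionnaire".
- **EEG Recording and Preprocessing** (nature and VR exposure alike). Participants may pause or end the session, and "any early termination will be documented and treated as dropout for EEG analysis". Resting EEG is scheduled at T0 and T1.
- **Statistical Methods**, estimand and analysis set. "All analyses will follow an intention-to-treat approach". The primary outcomes are "changes from preexposure (T0) to immediate postexposure (T1) in EEG alpha power", in cognitive performance and in ASRS. The primary contrasts are group × condition × time for alpha, and condition × time and group × time for cognition and ASRS.
- **Statistical Methods**, missing data. The main rule reads: "Missing data will primarily be handled within the mixed-model framework under a missing-at-random assumption". Two supporting checks are then named, in the statement that "sensitivity analyses will be conducted using multiple imputation and complete-case subsets", where the complete-case set needs data up to T1 and T9.

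**The concern.** T1 comes after the exposure. A VR participant who asks to stop therefore leaves the visit with a T0 value and no T1 value for EEG, the two tasks or ASRS. The cause is a reaction to the randomised exposure, and T0 measures do not record that reaction. The one instrument that could describe it, the VRSQ, is also completed after exposure and falls under the same cut-off. Cybersickness may then go unscored in the people who stopped because of it, although the Outcomes section plans to use VRSQ as a covariate where appropriate.

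The trial aims to say for whom each modality is suitable. If intolerant participants drop out of the T1 data, the real-versus-VR comparison drifts towards real nature versus VR among those who tolerate VR. T1 data that were never collected cannot be recovered by any later analysis plan.

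**Working it through.** **1. The plan's own figures.** The Power section gives alpha amplitudes of 6.93 (SD 2.04) and 7.88 (SD 1.83). The pooled SD is √((2.04² + 1.83²)/2) = 1.938, and d = 0.95/1.938 = 0.49, as stated. For the buffer, 64/(1 − 0.20) = 80, as stated; from the upper end, 72/(1 − 0.20) = 90. The buffer restores numbers and therefore precision. It does nothing about loss that depends on arm and outcome. Neither figure enters the bias below.

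**2. Following a VR participant who asks to stop.** T0 is observed and T1 is missing. The EEG plan analyses T1 − T0 change scores, so this participant has none. The complete-case set excludes the participant by definition. Multiple imputation, as usually run, assumes missing-at-random and fills T1 from people who tolerated the exposure. None of the named analyses covers loss that depends on the unobserved response.

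**3. Size for condition × time.** Let p be the share who stop and s the amount by which stoppers' true change falls short of that of non-stoppers, in SD of change. The mean over all randomised is the non-stoppers' mean minus p × s, so using non-stoppers alone overstates an arm by p × s. The bias in favour of VR is p(VR) × s(VR) − p(forest) × s(forest).

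The documents give no stop rate and no shortfall. Assumed: no stops in the forest, 5 to 20% in VR (2 to 8 of 40), and s from 0.5 to 1.0 SD.

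| VR stop rate | s = 0.5 | s = 1.0 |
|---|---|---|
| 5% | 0.025 | 0.05 |
| 10% | 0.05 | 0.10 |
| 20% | 0.10 | 0.20 |

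**4. Cross-check with a different model.** Let stopping depend on a latent tolerance that correlates r with the change. The shift in the observed VR mean is r × φ(c)/(1 − p), with c the normal quantile of p and φ the normal density. The last column is simulated under no true difference: 40 per arm, stopping in VR only, t test on observed change scores, 5000 runs, nominal two-sided 5%.

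| p | r | shift (SD) | type I error |
|---|---|---|---|
| 10% | 0.3 | 0.058 | 5.7% |
| 10% | 0.5 | 0.097 | 7.1% |
| 20% | 0.3 | 0.105 | 7.0% |
| 20% | 0.5 | 0.175 | 10.5% |

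With r = 0 the shift is zero.

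**5. Size for group × condition × time.** With no forest stops, the bias is p(ADHD) × s(ADHD) − p(control) × s(control), both within VR. If the products are equal, it is zero. At the extremes of the assumed ranges it is 0.20 × 1.0 − 0.05 × 0.5 = 0.175 SD, and the sign reverses if controls stop more.

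**The case against.** Much of the case on the other side stands.

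- **Direction.** A reader might infer that the comparison is biased towards VR as a matter of fact. The documents do not show this. It requires more stopping in VR than in the forest and worse unobserved outcomes in stoppers. That is plausible for cognition. For alpha, nothing in the documents says stoppers would have lower T1 values.
- **Frequency.** Stops may be few. Participants with previously limiting motion sickness or cybersickness, or with vestibular disorders, are excluded, and exposure is seated and capped at 20 minutes. Zero forest stops is the extreme assumption, since the EEG section lets participants in either arm end the session. The low end, 0.025 SD, is negligible.
- **Scale.** It is tempting to divide 0.20 by 0.49 and speak of 41% of the design effect. But 0.49 is a within-subject pre-post effect, whereas the primary alpha contrast is three-way, and a VR shift common to both diagnostic groups cancels there.
- **Scope of the rule.** The no-further-data sentence names participants who request to stop. Sessions ended by the researcher are covered explicitly only for EEG. The bar applies to that visit; nothing says stoppers leave T2 to T9. If they stay, later cognitive scores and the T9 ASRS could inform the models, although the resting EEG schedule names no later recording.
- **Intention-to-treat.** A reader might call this a contradiction. Missing outcomes do not in themselves breach analysis by randomised arm, and dropout for EEG can be read as missing data. The rule strains the principle rather than breaking it.
- **Missing-data analysis.** A missing-not-at-random analysis may sit in an analysis plan that is not shown. Its absence is not the finding.

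What these points leave intact is the collection rule itself. It creates missing T1 data for a reason related to the exposure, and no analysis plan can put those values back.

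**Conclusion.** The concern holds in a conditional form. As written, the protocol loses primary T1 outcomes in VR participants who ask to stop, and treats early termination in either arm as EEG dropout. This undermines the intention-to-treat aim and makes missing-at-random doubtful.

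Under the assumed stop rates and shortfalls, the condition × time comparison for cognition and ASRS would favour VR by about 0.03 to 0.20 SD. That range rests wholly on assumptions, because the documents give no stop rate. The direction for alpha is uncertain, and the group × condition × time contrast is affected only if stopping or shortfall differs by diagnosis. The protocol itself raises that possibility: the Exposure Duration section expresses particular concern about dropout among adults with ADHD.

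**What to change.** Leave the right to stop and all safety procedures as they are. Separate stopping the exposure from stopping data collection:

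1. Replace the no-further-data sentence. Anyone whose exposure ends early, in either arm and whoever ended it, is invited to complete T1, including resting EEG and, in the VR arm, the VRSQ. This is voluntary, and they are free to decline. Record the exposure duration and the timing of T1.
2. State that these participants remain in T2 to T9 unless they withdraw.
3. Reword the EEG section so that early termination does not exclude a T1 resting EEG that was obtained. Analyse everyone as randomised.
4. Report early stops by arm and diagnosis.
5. For T1 values still missing after a stop, add a delta-adjusted or tipping-point sensitivity analysis, with the adverse direction defined for each outcome.

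Setting missing T1 values equal to T0, or using EEG recorded before the stop, would not repair the primary T0-to-T1 outcome.

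The cost is a short wording change with ethics review, which the protocol already requires for substantial amendments. Some participants will decline T1, and some T1 assessments will follow a shorter exposure or a delay, so they will not match the standard immediate T1 exactly. The change is cheap before enrolment. Afterwards, T1 values that were not collected cannot be recovered.
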